**Phase 3: Reinforcement and role modeling (Week 9-12)**

**Responsible personnel**: The team will include 1 nurse, 1 psychologist, and 1 program coordinator.
**Competencies**: The nurse and psychologist will provide continued health education and emotional support, while the program coordinator will be in charge of managing the group activities and reinforcing family participation.
**Process**: In the final phase, the nurses and psychologist will reinforce the support behaviors of family members by sharing success stories from families who have completed the process. The nurses will also offer incentives to those who successfully complete the prenatal diagnosis. The program coordinator will organize group activities such as knowledge quizzes and family challenges to encourage participation. Each session will last 60 minutes and will be conducted weekly.
**Incident management**: If a participant experiences a setback, such as resistance from family members or emotional distress, the psychologist will provide additional counseling, and the nurse will assist with medical information or clarification. The program coordinator will facilitate family discussions to ensure everyone is on the same page and help resolve any disagreements or concerns.

**Evaluation and feedback:**

Regular evaluations will be conducted to track changes in the target families’ knowledge levels, prenatal diagnosis participation rates, and anxiety/depression levels. Feedback will be provided to adjust the intervention strategies in a timely manner.

This integrated intervention model, combining the Behavior Change Wheel theory and Family Health Theory, effectively leverages the power of the family to encourage high-risk pregnant women to participate more actively in prenatal diagnosis, providing support from the whole family and improving emotional wellbeing, ultimately leading to better pregnancy outcomes.

#### Standard care group

2.6.2

The standard care group will receive routine prenatal care without the additional mobile health intervention. Routine care includes basic information provided by medical staff at regular checkups, such as prenatal vitamins, ultrasound scans, and general prenatal education.

### Collection and screening of health education materials

2.7

#### Sources of health education materials

2.7.1

The health education materials used in this study will be collected from a variety of domestic and international platforms to ensure comprehensive and diverse content. These sources include well-known online platforms such as WeChat, Wikipedia, medical Q&A forums like “Doctor’s Q&A,” and specialized databases like ZhiNET. The collection will not be limited to text-based content but will also include video and graphic materials, which can better engage different learning preferences and facilitate a more accessible educational experience for the target audience.

All materials chosen for this study will be scientifically accurate and derived from credible sources. Specifically, medical documents and educational resources will be gathered from trustworthy online platforms, such as Baidu documents, authoritative medical websites, and peer-reviewed literature. Proper citations and references will be provided for all included materials to maintain academic integrity. Each selected piece of content will be evaluated for its factual correctness, reliability, and relevance to the study’s focus on birth defects, ensuring it provides up-to-date and valuable information to the public.

#### Screening of health education materials

2.7.2

After the collection and organization of the health education materials, a thorough screening process will be conducted. A panel of experts specializing in the field of birth defects will be responsible for reviewing the content of all materials. These experts, with deep knowledge in prenatal care, genetic counseling, and related areas, will evaluate the materials for scientific accuracy, clarity, and their ability to effectively communicate essential information to patients and the general public.

The experts will suggest any necessary modifications to improve the materials, ensuring they are scientifically sound and easily understood by a wide range of audiences. Any materials that do not meet the established criteria will be excluded from the final selection. The remaining high-quality materials will then be categorized into relevant areas such as awareness of birth defects, prevention strategies, prenatal care, and genetic counseling, among others. This classification will allow for the creation of targeted, informative push recommendations tailored to the specific needs of patients and the public.

The final selection of health education materials will be compiled into a comprehensive database, which will serve as a central resource for the study. This database will include key details for each material, such as the title, relevant links, sources, and material types (e.g., articles, videos, infographics). This resource will also be used to generate personalized push notifications to patients, offering them the most relevant and up-to-date educational materials. By ensuring that only high-quality, evidence-based resources are included, this process will support effective health education and help patients make informed decisions regarding birth defect prevention and care.

### Outcome measures

2.8

There is a total of nine outcomes in the study. Medical staff will use the Questionnaire Star web platform to distribute the questionnaire, and patients will complete the questionnaire online and be instructed by medical staff either in person (at the time of hospitalisation) or by telephone (after discharge). Patient demographic information will be collected through the case system and self-designed questionnaires. (**Table 1**)

**Table 1 T1:** Data collection components and collection timeline.

Type of research	Data collection component	Content	Timepoint	Month 3	After delivery
			Month 0		
Quantitative research	Sociodemographic variables	Sex, age, insurance status, place of residence, average monthly household income, educational level, parents’ education level, area of domicile,	✓		
	Demand for prenatal diagnosis	Willingness for diagnosis, plans for prenatal diagnosis within six months, or having undergone diagnosis	✓	✓	✓
	Pregnancy outcomes	Full-term birth, preterm birth, miscarriage, induced labor due to social factors, and induced labor due to chromosomal abnormalities	✓	✓	✓
	Health Knowledge and Birth Defect Prevention Knowledge Awareness	Self-designed questionnaire	✓	✓	✓
	Obstetric Complications	Gestational hypertension, postpartum hemorrhage, and low-quality infants.	✓	✓	✓
	Depression and anxiety	Patient Health Questionnaire-4 (PHQ-4)	✓	✓	✓
	Decisional Conflict	Decisional Conflict Scale (DCS)	✓	✓	✓
	Self efficacy	Decision Self-Efficacy Scale	✓	✓	✓
	Family Health	Family Health Scale-Short Form (FHS-SF)	✓	✓	✓
	Satisfaction	Decision-making participation satisfaction scale		✓	✓

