**Figure 5 f5:**
[figure not shown]
The process of randomization.

During group allocation, the order after sorting determines each subject’s group. Specifically, subjects in odd-numbered positions in the sorted order were allocated to the standard care group, while those in even-numbered positions were allocated to the intervention group. It should be noted that the subject identifiers remain in column A, but the actual group assignment is based on the sorted order in column B.

To ensure blinding, a single-blind design was adopted, where subjects were unaware of which group they were assigned to, but the evaluators were not blinded. To implement allocation concealment, the envelope method was used for group allocation. The procedure is as follows: Sufficient opaque envelopes were prepared, each marked with a unique identifier number corresponding to the subject’s identifier in column A of the Excel sheet. A small slip of paper with the group allocation information (Intervention Group and Standard Care Group) was placed inside each envelope. This allocation information corresponds to the envelope number, which matches the subject’s identifier in column A, ensuring that the envelope received by each subject corresponds to their assigned group based on the randomization process. The envelopes were then sealed.

After enrollment, subjects received an envelope in sequential order based on their subject identifier in column A. Each subject opened their envelope independently to reveal their group assignment. The distribution and opening of the envelopes were supervised by a designated person, and the process was recorded. All unused envelopes were securely stored to maintain the integrity of allocation concealment and the single-blind design.

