**Phase 2: Appointment scheduling and family support (Week 5-8)**

**Responsible personnel**: A team consisting of 2 nurses, 1 social worker, 1 psychologist, and 1 genetic expert.
**Competencies**: The nurses will guide participants in scheduling their prenatal diagnosis appointments, the social worker will facilitate family communication and ensure family members understand their supportive roles, the psychologist will provide emotional support and counseling to help manage anxiety and emotional concerns, and the genetic expert will provide specialized input on prenatal diagnosis and genetic counseling.
**Process**: During this phase, the nurses will assist pregnant women and their families in scheduling prenatal diagnosis appointments and provide support to ensure they understand the entire process. The social worker will educate family members on how to emotionally and physically support the pregnant woman. The genetic expert will host online lectures for the families to answer questions about the diagnostic process and boost their confidence in prenatal diagnosis. Each session will last 45 minutes and will be scheduled bi-weekly. The social worker will also send customized reminders to each family in the WeChat group, reminding them of the upcoming prenatal diagnosis appointment and key details while encouraging emotional regulation, such as, “Dear XX family, your prenatal diagnosis appointment is approaching, please be prepared and maintain a positive mindset!” For those who are anxious about the results or the process, the psychologist will provide counseling to help them manage their emotional concerns and complete the prenatal diagnosis with peace of mind.
**Incident management**: If a participant experiences logistical issues, such as scheduling conflicts or transportation problems, the social worker will step in to provide solutions or connect the participant with local resources to resolve these issues.

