#### Primary outcomes

2.8.1

The primary endpoints are the demand for prenatal diagnosis and pregnancy outcomes. Demand is defined as the perceived or expressed need, typically associated with changes in health status. Demand is measured at the individual level both before and after the intervention. A participant is considered to have a screening demand if they answer “yes” to at least one of the following three questions: willingness for diagnosis, plans for prenatal diagnosis within six months, or having undergone diagnosis. The overall demand is the union of these three items. For participants who report having been diagnosed, the researchers will verify the diagnosis by reviewing relevant documents or appointment cards.

Pregnancy outcomes include full-term birth, preterm birth, miscarriage, induced labor due to social factors, and induced labor due to chromosomal abnormalities.

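### Section 2.8 lets staff who are not blinded instruct women on the questionnaire behind the demand endpoint and does not keep the intervention team out, which may add desirability bias that differs by arm

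*Protocol article*

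**What the plan says.** **Collection.** Section 2.8 states that "Medical staff will use the Questionnaire Star web platform to distribute the questionnaire". Women complete it online and will "be instructed by medical staff either in person (at the time of hospitalisation) or by telephone (after discharge"). Table 1 schedules the demand items at Month 0, Month 3 and after delivery.

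**Endpoint.** Section 2.8.1 counts a woman as having demand if she answers yes to at least one of three items: "willingness for diagnosis, plans for prenatal diagnosis within six months, or having undergone diagnosis". Only the third is checked: "For participants who report having been diagnosed, the researchers will verify the diagnosis by reviewing relevant documents or appointment cards".

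**Blinding.** Section 2.4 calls the trial single-blind, "but the evaluators were not blinded". It also says: "Each subject opened their envelope independently to reveal their group assignment".

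**Contact with staff.** Section 2.6.1 gives the intervention arm three phases of contact over 12 weeks with nurses, psychologists and others. In Phase 2 "the nurses will assist pregnant women and their families in scheduling prenatal diagnosis appointments", and in Phase 3 nurses offer incentives for completing diagnosis. Section 2.6.2 gives controls routine care without this programme.

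**The concern.** Willingness and plans are statements of intention that no record can confirm, and either one alone meets the primary endpoint. Such answers are sensitive to who is involved when they are given. By Month 3 the intervention women have just finished 12 weeks in which hospital staff urged and rewarded the very behaviour the items ask about. Controls have no such relationship. If staff from that programme also guide the follow-up questionnaire, some women may answer yes to please them. Any such shift would favour the hypothesis and would occur mainly in one arm. The anxiety and depression, decisional conflict, self-efficacy, family health and satisfaction scales are open to the same influence.

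A smaller point concerns settings. Participants are women attending prenatal screening, and Month 0 and Month 3 are not tied to any hospital stay. The hospitalisation and discharge wording can describe the after-delivery form, but it leaves unclear how the Month 3 demand answer is obtained.

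**Working it through.** **1. The plan's own figures (Section 2.3).** Inputs: 72.8% versus 34%, two-sided alpha 0.05, power 80%, 1:1 allocation, 20% dropout.

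Unpooled two-proportion formula: n = (1.960 + 0.842)² × [0.34 × 0.66 + 0.728 × 0.272] / 0.388² = 22.02, rounded up to 23 per arm. With dropout, 23 / 0.8 = 28.75, rounded up to 29.

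Both figures reproduce. The sample-size arithmetic is not in question, and 23 and 29 per arm are used below.

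**2. What is stated and what is not.**
- Stated: medical staff distribute the questionnaire and instruct women on it; evaluators are unblinded; an unverified yes is enough; promotion and incentives go to one arm only.
- Not stated: who the instructing staff are, whether they belong to the intervention team, and what the instruction covers.

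**3. Illustration of size.** All of the following are assumptions, because the documents give no figure:
- There is no true effect, so true demand is 34% in both arms.
- A share q of intervention women without demand answers yes.
- No control woman shifts.
- Demand is compared by an uncorrected Pearson chi-square test at two-sided 0.05. Section 2.9 names chi-square only for demographic characteristics.

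Reported intervention rate = 0.34 + 0.66 × q. Rejection probabilities come from exact binomial enumeration.

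| q | Reported rates | Difference | Rejection, 23 per arm | Rejection, 29 per arm |
|---|---|---|---|---|
| 0 | 34.0% vs 34% | 0 | 4.9% | 4.6% |
| 10% | 40.6% vs 34% | 6.6 points | 7.4% | 7.5% |
| 20% | 47.2% vs 34% | 13.2 points | 15.1% | 16.6% |
| 30% | 53.8% vs 34% | 19.8 points | 28.2% | 32.2% |

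For scale, Section 2.3 cites an earlier trial with 53.4% versus 34%, a difference of 19.4 points. A 30% share would imitate an effect of that size.

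**4. What drives the illustration.** If controls shifted by a share r, the spurious difference would be 0.66 × (q − r), which is zero when q = r. Only the part of the shift that differs between arms matters. The table takes the extreme case r = 0.

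**The case against.** The strongest reply is that the mechanism is inferred. Women enter their own answers on a web platform, and being instructed may mean only help with opening and filling in the form. Section 2.8 refers to medical staff, the term Section 2.6.2 uses for those giving routine care to controls, whereas the intervention phases name their personnel by role. The text therefore fits clinic staff serving both arms. Delegation of tasks and questionnaire scripts are often left to a full protocol or to procedures. The shares of 10% to 30% are invented and assume no shift in controls. A woman who has opened her own allocation slip could tick yes alone on her phone. The Discussion already admits reporting bias from self-report.

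Most of this stands. A reader might infer that the intervention team administers the questionnaire, or that women give their answers to the nurse who coached them. The documents say neither. A reader might also take 7% to 32% as the trial's false-positive rate, but it is only the result of assumed shares, and not all of any such bias could be credited to this sentence.

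The reply does not remove the point. The article is not silent here: it fixes staff instruction as the collection mode, without limiting what the instruction covers or who gives it. The admitted reporting bias is general. It does not address bias that differs by arm or staff involvement in collection.

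**Conclusion.** The point holds as a risk that the plan leaves open. A subjective and mostly unverified primary endpoint is collected with instruction from staff who are not blinded, and the protocol does not separate them from those promoting diagnosis in one arm. This may add to desirability bias in the direction of the hypothesis. Its size cannot be derived from the documents. The range of about 7% to 32% at 23 to 29 per arm rests on no true effect, a shift of 10% to 30% among intervention women without demand, none among controls, and a chi-square test. The mismatch between the hospitalisation and discharge wording and the Month 0 and Month 3 visits is a separate matter of wording and is no evidence of bias. The change is worth making because it is cheap.

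**What to change.** In Section 2.8, replace the sentence on staff instruction with wording such as:

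*At Month 0, Month 3 and after delivery, women in both arms complete the questionnaire themselves through the Questionnaire Star link. Staff send the link and a fixed reminder, identical in both arms, and give technical help from a script only. Staff who deliver the intervention do not assist with the Month 3 and after-delivery questionnaires.*

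This also replaces the hospitalisation and discharge wording for Month 0 and Month 3.

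**Cost.** A short script and a reminder text. Extra staff should not be needed, since the platform is already online and the inclusion criteria require basic ability to use WeChat, but someone outside the intervention team must answer technical questions at follow-up. Expect a few more late or incomplete forms. With 23 women per arm left after the planned dropout, these should be followed up in the same way in both arms.

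**Limit.** The change reduces the bias but does not remove it, because women know their allocation and the endpoint remains self-reported.

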#### Primary outcomes

2.8.1

The primary endpoints are the demand for prenatal diagnosis and pregnancy outcomes. Demand is defined as the perceived or expressed need, typically associated with changes in health status. Demand is measured at the individual level both before and after the intervention. A participant is considered to have a screening demand if they answer “yes” to at least one of the following three questions: willingness for diagnosis, plans for prenatal diagnosis within six months, or having undergone diagnosis. The overall demand is the union of these three items. For participants who report having been diagnosed, the researchers will verify the diagnosis by reviewing relevant documents or appointment cards.

Pregnancy outcomes include full-term birth, preterm birth, miscarriage, induced labor due to social factors, and induced labor due to chromosomal abnormalities.

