### Sample size estimation

2.3

This study is a randomized controlled trial, where the intervention group will receive the mobile health intervention and the standard care group will receive standard care. The outcome measure is the prenatal diagnosis demand. Based on previous randomized controlled trials related to willingness to undergo screening for related diseases, the intervention group’s demand proportion is 53.4%, and the standard care group’s is 34%, showing an increase of approximately 19.4% (28). We predict that the mobile health intervention based on the Behavior Change Wheel theory and Family Health Theory may lead to a doubling of the demand proportion (38.8%), reaching 72.8% (29). The expected demand proportion for the intervention group is 72.8%, and for the standard care group is 34%. Using a two-sided test with α = 0.05, β = 0.2, and power (1-β) = 80%, the sample size ratio between the two groups is 1:1. After using the PASS software (version 2021) to calculate the relevant values, it was determined that 23 participants per group would be required. Considering a 20% dropout rate, the final sample size for each group is 29 participants, for a total of 58 participants.

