### Data analysis

2.9

This study uses IBM SPSS Statistics 24.0 software for quantitative analysis to ensure the accuracy and reliability of the statistical data. In terms of descriptive statistics, we present the baseline characteristics of the participants, with continuous variables being summarized by means and standard deviations or medians and interquartile ranges, while categorical variables are presented as frequencies and percentages. This statistical approach effectively summarizes the basic information of the sample, providing a solid foundation for subsequent analysis. The distribution of continuous data will be tested for normality. Normally distributed data will be presented as mean ± standard deviation (M ± SD), and non-normally distributed data as median (IQR). The Mann–Whitney U test will be used to compare changes in scale scores between baseline and endpoint between the two groups, while the Wilcoxon test will compare differences within each group. The chi-square test will compare the demographic characteristics of the two groups. Statistical significance will be set at p < 0.05, using a two-sided test.

In the case of missing data, assumed to be missing at random, baseline variables will be used as auxiliary variables, and missing data will be imputed using multiple imputation methods. Linear regression and logistic regression will be used for analysis, and the final combined analysis will complete the imputation process.

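### Pregnancy outcomes is a second primary endpoint with no sizing and no direction of benefit, and at 29 per arm it has little power for plausible effects

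*Protocol article*

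**What the plan says.** Section 2.8.1 (Primary outcomes) names two primaries: "The primary endpoints are the demand for prenatal diagnosis and pregnancy outcomes". Demand is a yes/no variable, positive if the woman is willing, has plans, or has already been diagnosed. The second primary is given only as a list: "Pregnancy outcomes include full-term birth, preterm birth, miscarriage, induced labor due to social factors, and induced labor due to chromosomal abnormalities". The section does not name an event of interest, a composite, an ordering, or which shift would count as benefit.

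Section 2.3 (Sample size estimation) treats demand as the only outcome: "The outcome measure is the prenatal diagnosis demand". All its inputs concern demand: 72.8% against 34%, two-sided 0.05, 80% power. It concludes that "it was determined that 23 participants per group would be required", and then: "Considering a 20% dropout rate, the final sample size for each group is 29 participants, for a total of 58 participants". It gives no rate, effect or power for pregnancy outcomes.

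Section 2.9 (Data analysis) sets one general threshold: "Statistical significance will be set at p < 0.05, using a two-sided test". It ties the chi-square test to demographic characteristics and names no test for either primary. It does not say whether one or both primaries must succeed.

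**The concern.** The sizing and the endpoint list do not match. Half of the primary objective carries no planned information, and the endpoint cannot be read in the way the article wants to use it.

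The intervention is meant to raise uptake of prenatal diagnosis in women whom the Introduction describes as being at raised risk of fetal anomaly. More diagnosis could mean more inductions for chromosomal abnormality, which is one of the five categories. A difference across the list could then arise because the intervention worked, and still look adverse. The abstract's Discussion and section 2.6.1 speak of improving pregnancy outcomes, but the endpoint does not define improvement.

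At stake is one of the two headline conclusions. A null result would say little because power is low. A significant overall result would have no agreed direction.

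**Working it through.** **1. The plan's own figure.** Inputs from section 2.3: p1 = 0.728, p2 = 0.34, two-sided α = 0.05, power 0.80. With unpooled variance,

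n = (1.960 + 0.842)² × [0.728 × 0.272 + 0.34 × 0.66] / (0.388)² = 7.849 × 0.4224 / 0.1505 = 22.02, so 23 per arm.

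Dropout: 23 / 0.8 = 28.75, so 29 per arm. Both stated figures reproduce, for demand only. (The pooled-variance formula gives 25.)

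**2. Pregnancy outcomes reduced to one adverse yes/no event.** The article gives no rates, so the following are assumptions. Power is by exact enumeration of both binomials at 29 per arm, no dropout, two-sided 0.05:

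| Assumed rates | Fisher | Uncorrected chi-square |
|---|---|---|
| 15% vs 5% | 8.5% | 25.4% |
| 25% vs 10% | 20.0% | 32.4% |
| 30% vs 15% | 18.0% | 26.9% |

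Sample size for 80% power to detect a halving, from n = [1.960√(2p̄(1−p̄)) + 0.842√(p1(1−p1) + p2(1−p2))]² / (p1−p2)²:

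- 10% vs 5%: 435 per arm
- 15% vs 7.5%: 278
- 20% vs 10%: 199
- 30% vs 15%: 121

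Against 29, the shortfall runs from 121/29 ≈ 4-fold to 435/29 = 15-fold.

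**3. All five categories tested together (4 df).** Illustrative assumption, in the order of the article's list: 75/12/5/4/4% under standard care and 80/8/3/2/7% under intervention. The mean proportions are 0.775, 0.10, 0.04, 0.03 and 0.055. Expected counts per arm of 29 are 22.5, 2.9, 1.2, 0.9 and 1.6, so four of the five are below 5. The noncentrality is λ = 29 × Σ[(pc−p̄)² + (pt−p̄)²]/p̄ = 29 × 0.0295 = 0.85, which gives about 10% power. For 80% power, λ must be about 11.9, that is w = √(11.9/58) ≈ 0.45.

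**4. What two primaries imply.** The article leaves the rule open, so both readings are shown.

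- Either suffices, independent tests, each of full 5% size: 1 − 0.95² = 9.75% (at most 10% whatever the dependence).
- Either suffices, but pregnancy outcomes are tested by Fisher as a binary event: its true size at 29 per arm is about 0.1% at a 5% event rate and 0.9% at 10%. With demand at a nominal 5%, the family-wise error is 1 − 0.95 × 0.9987 ≈ 5.1% to 1 − 0.95 × 0.9913 ≈ 5.8%.
- Both required: α is not inflated, but joint power cannot exceed that of the pregnancy endpoint, about 9% to 32% under the rates in step 2.

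**5. Cost of keeping both with a split α.** Exact chi-square power for demand at 0.025 instead of 0.05 falls from 78% to 68% at 23 per arm, and from 86% to 79% at 29 per arm.

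**The case against.** A reader might infer that both primaries are each tested at 0.05, that success on either counts, and that the false-positive rate is therefore nearly doubled. The article does not support this as a statement of fact. It sets one general threshold, assigns no test to either primary, and is silent on the success rule. A multiplicity rule may stand in an analysis plan that is not shown. Near-doubling also needs a pregnancy test of close to nominal size, which does not hold for Fisher's test at low event rates (step 4). This objection stands, so about 10% is a conditional ceiling and the point does not rest on it.

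A reader might go further and reach 18.5% from four tests (1 − 0.95⁴), because Table 1 lists both endpoints at Month 3 and after delivery. That would need four independent confirmatory tests. The article declares no such tests, demand at the two visits comes from the same women, and a pregnancy ends only once.

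It can also be said that the formal objective is neutral, since the Objective and section 2.1 speak of evaluating impact. Nor does the article show that inductions for chromosomal abnormality will rise; among 29 women the change could be nil. Both remarks are fair: the category could rise, not must. They do not rescue the endpoint, because without a defined event or direction even a neutral evaluation has no stated way to be read.

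Section 3 does concede a limited sample, but as a source of regional and selection bias, not as a limit on this endpoint.

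**Conclusion.** The point holds on what the article itself fixes: two primaries, sizing on one, and a second that is an undirected list. An unseen analysis plan could add a testing order, but it could not change the fact that 29 per arm was derived for demand only.

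Power for pregnancy outcomes is about 9% to 32% for the two main assumed contrasts (15% vs 5% and 25% vs 10%), and about 10% for an illustrative five-category test. These figures rest on assumed rates and on no dropout. At 29 per arm, only extreme differences would be detected reliably: by the normal approximation, an adverse rate of 30% would have to fall to about 3% for 80% power, and from 10% or 20% no reduction reaches it. The claim is therefore very low power for plausible effects, not that a test is impossible. The lack of direction does not depend on any assumed rate.

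**What to change.** - Make demand for prenatal diagnosis, as defined in section 2.8.1 and sized in section 2.3, the single primary endpoint, tested at two-sided 0.05. The wording must say demand. A reader might take completed prenatal diagnosis as the natural primary, but that is only one of the three parts of demand, and the 34% and 72.8% behind the sample size would no longer apply.
- Make pregnancy outcomes secondary. Report each category by arm as a risk difference with a 95% confidence interval, without a confirmatory test.
- Show induction for chromosomal abnormality separately, as a possible consequence of diagnosis.
- Draw no confirmatory conclusion that pregnancy outcomes improve.

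The change is one of protocol wording. It needs no extra participants or data, and the sample size stands as calculated. It should be made before outcomes are compared by arm. The downside is that one headline claim becomes exploratory. Keeping both primaries with a split α would instead cost demand the power shown in step 5 and leave the pregnancy endpoint undirected.
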